
### Data management

All data collected throughout the project will be de-identified at the point of extraction. A unique study and participant ID code will be assigned to each record. The linkage file connecting identifiers to participant information will be held securely by the Principal Investigator (SW).

Data entry and coding procedures will follow standardised protocols. Range checks and validation rules will be applied to data fields to prevent entry errors and maintain data consistency.

All digital data will be stored on encrypted, password-protected servers compliant with institutional data security policies. Access to the data will be limited to authorised personnel only. Physical files will be stored in locked filing cabinets within secure, access-controlled research offices.

Further detail regarding data handling procedures—including the data management plan, coding framework, and quality assurance processes—is available from the study team upon reasonable request and is maintained in the internal project documentation, separate from the protocol.

The scope of the study does not warrant the additional oversight of a Data Monitoring Committee (DMC). Instead, data oversight and integrity monitoring will be managed internally by the study team under the supervision of the PI, in line with institutional governance procedures.

#### Dissemination policy

There are no publication restrictions imposed by the sponsor or any funding body. The investigators retain the right to publish and disseminate findings regardless of the outcomes.

Authorship will be determined based on the NMHRC authorship guidelines. Professional medical writers will not be used in the development of the final publication. Participant-level de-identified datasets and statistical code may be made available to qualified researchers on reasonable request, subject to ethical approvals and data sharing agreements that ensure participant confidentiality and appropriate data use.

## Discussion

The overarching goal of this project is to implement and report on changes in the service model in our multidisciplinary sleep service, specifically a new model of care that incorporates a “Direct to Psychology Insomnia” referral pathway, that includes a “Stepped Care” treatment approach that utilises digital, group therapy, and intern and senior therapist-led interventions. Other multidisciplinary teams have envisioned similar Allied Health-led referral pathway plans to beneficial effect [43, 44]. Results from this study will highlight the potential for Direct to Psychology referral pathways in reducing the clinical burden on physicians and expediting patient access to first-line treatment for insomnia. Patient outcomes, satisfaction, and service-based evaluation tools are embedded in this project to compare the model of care to treatment as usual. We anticipate that if shown to be acceptable, the findings from this study will inform future iterations and enhancements to the model of care, including the scalability to apply the model to other services.

Streamlining sleep psychology interventions into a stepped care treatment approach will allow patients to access the appropriate level of care based on their level of acuity and clinical presentation, with the model being flexible enough for patients to be expedited to more resource intensive levels of care based on treatment response. The new model of care will utilise technology as part of a Stepped Care model to provide a platform for more efficient service delivery, backed by expert clinician oversight in order to provide care to more patients within existing resources. We expect the new evidence-based model of care will substantially reduce wait times for patients and provide timely access to effective Psychological treatment, resulting in non-inferior clinical outcomes. We posit that this dynamic approach to sleep disorder management will result in better patient access and outcomes, leading ultimately to reduced societal burden from reduced productivity and health care costs due to untreated sleep disorders.

By incorporating consumer and stakeholder engagement throughout, we will ensure the model of care developed is acceptable to all stakeholders. By sharing and disseminating the learnings from this program to primary health services and the general community, we aim to increase engagement in evidence-based digital therapies, thus increasing the baseline sleep health of our community and reducing reliance on acute hospital services. By increasing access to, and promoting the availability of evidence-based digital therapies, we can empower consumers to engage with their own self-management, potentially reducing referrals into the acute hospital system.

Given the real-world dataset and service imperatives to be utilised, there are potential limitations to this study, including challenges in recruiting evenly to all intervention arms, and unplanned but typical participant attrition during the self-guided portion of the digital intervention, both of which may impact the results. We plan to address these challenges for those assigned to digital intervention via bi-monthly therapist or intern ‘check-in calls’ to address barriers to engagement, and to make administrative changes to triage and intake processes to flow more participants to the digital arm if indicated. However, the study is adequately powered to compensate for these factors and we anticipate that the Direct to Psychology referral pathway and Stepped Care treatment model will be acceptable to patients and clinicians and overall will improve patient care within the health system.

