*How effective was the model of care in achieving its intended outcomes?*	**Effectiveness** – impact on outcomes and quality of life/economic outcomes	**Primary outcomes** *Service Access Measures* • Average number of occasions of Service within Sleep Psychology service under ‘old’ model compared to ‘new’ model of care • Percentage of new patient activity under ‘old’ model compared to ‘new’ model of care • Average wait-time to access a first appointment with Sleep Psychology from date of referral under ‘old’ model compared to ‘new’ model of care • Average time to discharge from first appointment to final appointment with Sleep Psychology under ‘old’ model compared to ‘new’ model of care • Percentage of patients discharged from psychology *Patient-related Outcomes* • Change scores on clinical outcome measures pre- to post- treatment on clinical outcome measures (ISI, DASS-21, K10 and EQ-5D-5 L) comparing patients treated under ‘old’ model versus ‘new’ model of care • % patients treated adequately at each level of Stepped Care • Differences in patient characteristics (age, sex, geographical location, presenting issue) between those who are adequately treated at each level of the new model of care (moderation analysis) *Economic Outcomes* • Quality-adjusted life year calculations as a measure of cost-effectiveness of the ‘new’ model of care compared to the ‘old’ model of standard care **Secondary outcomes** *Patient satisfaction* • Patient satisfaction measure (SRS) post- treatment comparing patients treated under ‘old’ model versus ‘new’ model of care *Patient satisfaction with digital intervention* • Patient reported ease of access to digital intervention • Acceptability and relatability of the online program/service provided (rated by patients), including: i. motivation to access online treatment (diversion from public hospital services for insomnia treatment) ii. understanding of intervention materials iv. perceived change in sleep problem • Differences in patient characteristics (age, sex, geographical location, presenting issue) between those who complete the digital intervention compared to those who do not complete	Significantly fewer occasions of service under new model of care Significantly greater % new patient appointments under new model Significantly shorter wait-time to first appointment under new model Significantly shorter time to discharge under new model Outcomes are non-inferior under new model of care; upper bound 95%CI on outcome measures is less than MCID MCID is achieved on outcome measures by > 80% patients at each level The ‘new’ model is more cost effective Patient reported satisfaction is non-inferior under new model of care; upper bound 95%CI is less than MCID > 90% patients report positive experiences	Patient qualitative and quantitative surveys Medical Record Patient registration system

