### Statistical analysis

The project will employ a mixed methods approach. Qualitative surveys for patients, multidisciplinary staff, and referrers was undertaken pre-service change to ascertain the acceptability of the digital therapy, as well as familiarity, access, confidence, and relatability of this treatment option [25]. Post-implementation surveys will also be undertaken on these same metrics. Quantitative data will be collected pre- and post-service change to ascertain treatment effectiveness in terms of clinical outcome measures, as well as service measures of interest such as patient flow, occasions of service and program engagement. Based on similar studies [40], and allowing for some incomplete data, we expect to have data for approximately 110 participants from each pre- and post- time period, resulting in a sample of 220 participants overall who will be suitable for the Direct to Psychology pathway. To assess wait times, participants will be categorised into four groups based on the time-period (pre/post implementation) and whether they met eligibility criteria for the Direct to Psychology pathway. Differences in wait times between the groups will be assessed using a one-way Analysis of Variance (ANOVA) and linear regression modelling. In a one-way ANOVA study, a sample of 220 participants, divided by 4 groups, achieves 80% power with a significance level of 0.05 to detect a moderate-large effect size (Cohen’s f) of 0.25 [41]. The effects of other variables of interest and potential confounders (patient characteristics, diagnosis,) will be tested in multivariable models. For differences in patient outcome measures pre- and post- intervention when comparing pre- and post- service change, the mean between-group difference and 95% confidence interval (CI) will be calculated. As this aspect of the evaluation is a non-inferiority trial (that is, we expect clinical outcomes to not be reduced due to the service change), the criteria adopted to determine non-inferiority will be if the upper bound 95%CI on each clinical outcome measure was less than the minimal clinical important difference (MCID). Quantitative data measuring pre- and post- service change outcomes on key indices of patient service satisfaction, service characteristics (e.g., occasions of service); as well as referrer and staff service satisfaction, and engagement with digital therapies, will be evaluated via univariate statistical tests where indicated such as independent samples t-test (or nonparametric equivalent), and categorical comparisons will be evaluated using Pearson’s chi-square. The distribution of outcome measures will be assessed, and appropriate transformations will be applied for use in modelling. Differences between group means will be tested using generalised linear regression modelling. Health related quality of life will be measured pre- and post- implementation using the EQ-5D-5 L. Population norms for EQ-5D-5 L Australia will be used to value the data set [42].

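### The claim that power compensates for uneven arms and digital attrition rests on a wait-time calculation that these factors do not enter

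*Protocol article*

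**What the plan says.** The limitations paragraph of the Discussion lists two threats: the first is "challenges in recruiting evenly to all intervention arms", the second "unplanned but typical participant attrition during the self-guided portion of the digital intervention". It accepts that both may affect the results, and describes check-in calls and changes to triage as countermeasures. It then adds: "However, the study is adequately powered to compensate for these factors".

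The one power statement is in Statistical analysis. The test is for wait times: "Differences in wait times between the groups will be assessed using a one-way Analysis of Variance (ANOVA) and linear regression modelling". The four groups are formed by period (before or after implementation) and by eligibility for the Direct to Psychology pathway. The stated result is that "a sample of 220 participants, divided by 4 groups, achieves 80% power with a significance level of 0.05 to detect a moderate-large effect size"; the value given for Cohen's f is 0.25. The expected data are about 110 participants per period, described as allowing for some incomplete data, with no rate given.

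Patient-related outcomes (under Primary outcomes) and Table 1 (Effectiveness) also make two other things primary:

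- Change on ISI, DASS-21, K10 and EQ-5D-5L, judged by non-inferiority: "the criteria adopted to determine non-inferiority will be if the upper bound 95%CI on each clinical outcome measure was less than the minimal clinical important" (that is, the MCID).
- The proportion adequately treated at each of the four levels, with the Table 1 target "MCID is achieved on outcome measures by > 80% patients at each level".

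Neither comes with a power or precision figure.

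**The concern.** The Discussion makes a positive claim about power, and the only calculation in the article concerns another outcome and other groups. The arms in the limitations paragraph are the treatment levels: the same paragraph speaks of steering more participants to the digital arm. The ANOVA groups are not those levels. Dropout during the digital programme happens after the wait has ended, so it cannot change a wait-time comparison.

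The two factors act on post-treatment scores and on the numbers within each level, that is, on the non-inferiority and per-level outcomes. A reader who takes the sentence at face value could read a non-inferiority test that fails, or a level that misses 80%, as evidence against the model or that level, when the data may be too few to tell. The sentence also presents attrition as a matter of numbers, whereas loss related to response biases the comparison at any sample size.

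**Working it through.** **1. The plan's own figure.** Inputs from Statistical analysis: N = 220, k = 4, alpha = 0.05, f = 0.25. Noncentrality λ = N·f² = 220 × 0.0625 = 13.75, with 3 and 216 degrees of freedom. The noncentral F gives power of 88.4%, against the stated 80%. For 80% power, 179 patients suffice (180 if balanced), so there is room for a loss of (220 − 180)/220 = 18%. The stated figure is conservative, and an undisclosed allowance for incomplete data might explain it. This reserve belongs to a balanced wait-time comparison and to nothing else.

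**2. Do the two factors enter that calculation?**

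| | Wait-time ANOVA | Non-inferiority on change scores | Per-level target |
|---|---|---|---|
| Groups | period × eligibility | old v new model | four treatment levels |
| Outcome fixed | before digital dropout | after treatment | after treatment |
| Digital attrition acts on it | no | yes | yes |
| Level sizes act on it | no | not on total n | yes |
| Power or precision shown | yes | no | no |

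**3. What 110 per period gives for non-inferiority.** Assumptions: true difference 0, equal SDs, two-sided 95% CI (one-sided 0.025), 110 v 110.

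Standard error in SD units = √(1/110 + 1/110) = 0.135. Smallest margin with 80% power = (1.96 + 0.84) × 0.135 = 0.38 SD.

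| Margin (SD) | Power, one measure |
|---|---|
| 0.3 | 60% |
| 0.4 | 84% |
| 0.5 | 96% |

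For ISI, the only threshold in the article is 8 points. If that is the margin and the SD is 5 to 8 (assumed), n per period = 2 × (1.96 + 0.84)² × (SD/8)², which is 7 to 16. Power exceeds 99.9% even at 55 v 55. No MCID is stated for DASS-21, K10 or EQ-5D-5L, so for them adequacy cannot be judged either way.

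**4. What the per-level target can show.** Assumption: 110 new-model patients split evenly over four levels, 110/4 = 27.5, so 27 or 28 each.

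- Half-width of a 95% CI around 80%: 1.96 × √(0.8 × 0.2/28) = 14.8 points; with 27 patients, 15.1 points.
- Showing a rate above 80% with 28 patients (exact binomial, one-sided 0.025) needs at least 27 successes: P(X ≥ 27 | 0.80) = 0.015. If the true rate is 90%, P(X ≥ 27) = 0.9²⁸ + 28 × 0.1 × 0.9²⁷ = 0.215, so power is about 22%.
- With 19 patients all must succeed, and power at a true 90% is 0.9¹⁹ = 14%. With 14 patients no result suffices, since 0.8¹⁴ = 0.044 exceeds 0.025.
- If the target is only that the observed rate exceeds 80%, a level of 28 with a true rate of 85% meets it with probability 0.765, and so misses it about 24% of the time by chance alone.

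**The case against.** **The full protocol or analysis plan may size these outcomes.** It may, and the absence of such a calculation from an article is no fault. The point is narrower: the article makes a claim that the calculation it shows cannot carry.

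**The wait-time calculation has slack, and 110 already allows for some incomplete data.** Both are true. The slack does not transfer to a confidence bound against a margin or to a proportion within a level. The allowance is unquantified and tied to neither outcome. It does mean that one cannot say attrition was ignored, and taking a further loss off the 110 might count it twice, so the figures above do not.

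**A reader might infer that the non-inferiority tests are underpowered.** The documents do not support that. ISI with a margin of 8 has ample power, and for the other measures it depends on margins and SDs that are not stated.

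**A reader might infer that all four measures must pass, so that joint power is much lower.** The criterion is applied to each measure, and nothing says that overall success requires all four.

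**A reader might infer that uneven levels would sharply cut the chance of meeting the target at every level.** No level sizes are given. Such a calculation also turns largely on whether exactly 80% is attainable at the sizes chosen, because exactly 80% counts as a miss.

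**The 110 is not the number entering the levels.** This stands. The 220 are patients suitable for the direct pathway, whereas the Standard care section lets other psychology referrals into the levels, and patients may move between levels. Actual numbers may be larger, and the per-level figures are an illustration.

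**The 80% figure is an evaluation target, not a hypothesis test.** This also stands. It is why the remedy is an interval and a caution on reading, not a larger sample.

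**Conclusion.** The concern holds in a limited form. The statement that power compensates for uneven arms and digital attrition has no support in the article for the primary outcomes that those factors affect. The only calculation, which gives 88.4% power by recomputation, concerns wait times, which they do not touch.

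The size depends on the outcome. It is no practical problem for ISI if the margin is 8. It is undetermined for DASS-21, K10 and EQ-5D-5L, where 80% power needs a margin of about 0.38 SD at 110 v 110 with no true difference. It is clearest for the per-level target, with about ±15 points and about 22% power at a true 90%, given the assumed even split of 110. Whatever the numbers, power does not correct bias from dropout that depends on response. This is a correction of a claim and of how results are read; it does not show that the design fails.

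**What to change.** - In the limitations paragraph of the Discussion, delete the claim that power compensates for uneven arms and attrition, and limit the power statement to the wait-time comparison. If the full protocol holds a calculation for the clinical outcomes, cite it for those outcomes only.
- Report the proportion reaching the MCID at each level as an estimate with a 95% CI beside the 80% target, and state that a missed target in a small level is not by itself failure of that level.

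The cost is a change of wording and one interval per level, with no extra patients. The downside is a less favourable statement of what the study can show.

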## Data Availability

Data and materials that support this manuscript are available from the corresponding author, SW, upon reasonable request.

## Abbreviations

AASM: American Academy of Sleep Medicine
ACTRN: Australian and New Zealand Clinical Trials Registry
ASA: Australasian Sleep Association
CBT: cognitive behavioural therapy
CBTi: Cognitive Behaviour Therapy for Insomnia
COMISA: Comorbid Insomnia and Obstructive Sleep Apnoea
CI: Confidence Interval
CPAP: Continuous Positive Airway Pressure therapy
DASS-21: Depression Anxiety and Stress Scale
DSM-V-tr: Diagnostic and Statistical Manual
EQ-5D-5L: EuroQol
HREC: Human Research Ethics Committee
ISI: Insomnia Severity Index
ICD-11: International Classification of Diseases
K10: Kessler Psychological Distress Scale
MAS: Mandibular Enhancement Splint
MCID: minimal clinical important difference
MoC: Model of Care
OSA: Obstructive Sleep Apnoea
SRS: Session Rating Scale
StaRI: Standards for intervention Reporting Implementation Studies
